### Data Analysis

To understand SOAR preferences and usability, interview transcripts will be cleaned and confirmed for accuracy before being uploaded into the qualitative data management program, Dedoose, where data will be coded and categorized [42,43]. First, the research team will separately analyze each transcript using predefined codes and open coding, and then discuss coding to confirm alignment and coding distinctions in order to clarify codes [16]. Second, using a thematic approach [44], researchers will analyze the coded transcripts to identify SOAR preferences and usability themes as an iterative process. An additional comparative analysis based on age was conducted to identify any distinctions [44-46]. These discrepancies will be resolved by agreement during research team discussions.

### Evaluating the Feasibility of SOAR for Transgender Women

After SOAR has been tailored, in aim 2, we will conduct a pilot study of the intervention using a 1-arm design to determine feasibility, acceptability, willingness, and safety for transgender women (SOAR study design; Figure 1). Also, we will collect data on ART adherence (viral load) and relationship communication to establish a preliminary understanding of outcomes and implementation of measures in a larger study.

We will recruit transgender women (N=20) living with HIV and suboptimally adherent to ART (missed at 2 doses over 2 weeks), to complete the intervention. Additionally, participants must have been in a romantic relationship with a man for more than 1 month and live in Eastern Cape. For screening, participants will complete a rapid HIV viral load test to confirm HIV status.

There will be 5 participants per group for a total of 4 groups. All participants will be recruited and screened into the study by the trained study coordinator, and all recruitment activities will occur at transgender community–focused events. During the consent process, participants will be provided a general overview of the study and informed about the number of study sessions and expected behavioral and biomedical data collection procedures. As in aim 1, all participants will receive a travel reimbursement and refreshments.

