## Introduction

### Background

HIV infections among transgender women are 2.2 higher than gay, bisexual, and other men who have sex with men in sub-Saharan Africa due to syndemics consisting of stigma and discrimination that perpetuate violence and victimization, limiting access to HIV prevention and treatment [1-4]. In South Africa, the HIV incidence for transgender women is 31 cases per 100-person years, with studies showing limited pre-exposure prophylaxis (PrEP) and antiretroviral therapy (ART) access and adherence. Based on other African studies, only an estimated 25% of transgender women are virally suppressed [5-7]. HIV prevalence among transgender women in South Africa mirrors the realities that they share with their peers in other Global South settings, with a 52% mean prevalence documented in 3 South African cities [8]. Transgender women’s health and safety remain compromised in South Africa, inhibiting their ability to engage in HIV services to lower transmission risk and improve their overall wellness, and compounding these health outcomes are poor relationship dynamics.

Being in an unhealthy or imbalanced relationship for transgender women can lower their HIV testing behaviors and increase rates of condomless anal intercourse with partners to create trust and intimacy [9-13]. Fear of partner rejection or loss and intimate partner violence may lead transgender women to limit or halt ART use to conceal their serostatus from partners [14-16]. Further, studies increasingly show that transgender women experience negative outcomes of relationship stigma (when partners fear being romantically associated with someone who is stigmatized), which in turn has hindered their ability to discuss HIV treatment with them [15,17]. Although studies with transgender women in South Africa are limited, in the United States, relationship dynamics for transgender women influence HIV risk, in the same ways they do for cisgender women and sexual minority men [17-21]. Additional factors hindering HIV prevention and treatment discussions that transgender may have with a partner include living with them, drug use, alcohol use, education level, and low self-efficacy to use condoms [18]. In sum, cisheteronormative social structures and power dynamics have been shown to result in increased marginalization, increased susceptibility to intimate partner violence, and increased risk of mental issues among transgender women, all hindering HIV prevention and treatment [22-24].

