### Procedures

#### Overview

Once enrolled, participants will complete a behavioral survey on REDCap. These measures cover HIV, sexuality, relationship stigma and discrimination, communication in relationships, and HIV prevention and treatment behaviors [47-53]. They will also complete syphilis testing using a rapid diagnostic test (Abbott Determine Syphilis TP), blood draw for HIV viral load, and urine collection for *Chlamydia trachomatis* and *Neisseria gonorrhea* testing. All measures will be administered by study staff.

Afterward, participants will receive training in Zoom, and their smartphones will be assessed and set up for Zoom compatibility. Participants will be notified that they will receive an SMS reminder 12 hours before each session, and then 1 hour before each session, they will receive an SMS with the Zoom link for that session. Also, participants will be informed that during the intervention they will be asked to complete an action plan, and they will receive a partner referral letter via SMS or in paper form (their choice) at the start of the study and can request the letter throughout the study. The referral letter describes the availability of local HIV and mental health services. Each participant will be informed that they will complete 1 SOAR session per week for 5 weeks with 2 check-in sessions afterward.

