#### Participants

For both study aims, all transgender women will be over the age of 18 years, be in a relationship for more than a month, own a smartphone, be comfortable with group discussions about HIV, and be HIV-positive with confirmatory testing using OraQuick (OraSure Technologies) during screening. We will enroll with racial diversity to ensure the representation of multiple voices. Our relationship criteria require participants to have a self-reported romantic or emotionally connected partnership with another individual of any sex or gender, and partners must be either HIV-negative or of unknown status. Additionally, all participants need to live in Eastern Cape and suboptimally adhere to their HIV treatment [66].

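### Two different tests are named to confirm HIV status at aim 2 screening, and one of them, viral load, cannot confirm it in a treated woman who is undetectable

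*Protocol article*

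**What the plan says.** Two sections of the protocol article set out how HIV status is established at screening.

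- **Evaluating the Feasibility of SOAR for Transgender Women** (aim 2): "For screening, participants will complete a rapid HIV viral load test to confirm HIV status".
- **Participants**: the paragraph opens "For both study aims, all transgender women will be over the age of 18 years" and goes on to require that they "be HIV-positive with confirmatory testing using OraQuick (OraSure Technologies) during screening".

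The abstract adds that aim 2 recruits under the aim 1 methods and eligibility criteria, which also brings aim 2 under the OraQuick rule.

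The aim 2 section describes the target group as women "living with HIV and suboptimally adherent to ART (missed at 2 doses over 2 weeks), to complete the intervention". No viral load threshold forms part of that criterion.

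Viral load also appears as a study measure. Under Procedures, Overview, women who have already enrolled have a "blood draw for HIV viral load". The section on relationship, adherence and biomedical measures has it collected from baseline through follow-up.

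**The concern.** Two tests are given the same job at the same step, and the article does not say which one decides or what follows if they disagree.

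They are not interchangeable in this population. Participants are women on ART. The protocol itself relies on the fact that treatment can make virus undetectable: the U=U message appears in the Introduction and in the Theoretical Framework as part of what SOAR teaches. A woman living with HIV who is undetectable would return a viral load result that does not confirm her status.

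Two things that the pilot is meant to learn would be affected if the viral load result decided entry:

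- **Recruitment.** The Feasibility section counts the ability to recruit as part of feasibility. Losing eligible women to an unsuitable test would make recruitment look harder than it is.
- **Viral load change.** Selecting on a detectable value at entry tends to be followed by lower values without any intervention effect, and a 1-arm design has no comparison group to separate the two. The planned efficacy study is to look at viral load, so the pilot's values may be carried forward.

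**Working it through.** **1. The plan's own figure.** The aim 2 sample is 20 ("We will recruit transgender women (N=20) living with HIV"), built from the group structure ("There will be 5 participants per group for a total of 4 groups"): 5 × 4 = 20. This reproduces exactly. There is no power calculation, and nothing below changes the sample size.

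**2. Could the screening test simply be the baseline measurement?** No. The baseline viral load is a separate blood draw after enrolment. The only purpose given for the screening test is to confirm HIV status.

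**3. Does the adherence criterion already remove suppressed women?** No. It concerns missed doses. The text is garbled (a word seems to be lost after 'missed at'). Read as exactly 2 missed doses, and assuming once-daily dosing, 12/14 = 85.7% of doses were taken. If the lost word is 'least', 85.7% is a ceiling. Either way, a woman can meet the criterion and be suppressed.

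**4. What would follow if only a detectable viral load counted as confirmation?** Let p be the share of otherwise eligible women who are suppressed.

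- Expected number unconfirmed among 20 such women: 20 × p
- Probability that at least one of 20 is unconfirmed: 1 − (1 − p)^20
- Number to screen so that 20 are expected to be confirmed: 20/(1 − p), rounded up

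The only suppression figure in the article is in Background: "only an estimated 25% of transgender women are virally suppressed". It is attributed to other African studies and is not specific to suboptimally adherent women. The other values of p are assumptions that show the range.

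| p | Expected unconfirmed of 20 | P(at least 1) | Number to screen for 20 |
|---|---|---|---|
| 5% (assumed) | 1 | 0.642 | 20/0.95 = 21.05, so 22 |
| 10% (assumed) | 2 | 0.878 | 20/0.90 = 22.2, so 23 |
| 25% (Background figure) | 5 | 0.997 | 20/0.75 = 26.7, so 27 |
| 50% (assumed) | 10 | above 0.999 | 20/0.50 = 40 |

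**5. What if OraQuick decides?** A woman's viral load then plays no part in confirming her status, and the loss in step 4 does not arise.

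**The case against.** The strongest reply is that exclusion is inferred. The article nowhere says that an undetectable result screens a woman out. The Participants section is the eligibility section, covers both aims and names OraQuick. The aim 2 sentence could be a loosely worded extra test, and how an undetectable result is handled may be in the full protocol or in Figure 1, which is not available here. This stands as far as consequences go: they are conditional on the viral load result having decided eligibility. It does not remove the conflict, because the aim 2 sentence gives confirmation of status as the test's purpose.

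Three stronger readings are tempting and are not supported.

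- **That the pilot enrolled only viremic women.** No rule or result in the article says so.
- **That screening losses explain why 14 women rather than 20 are reported.** The article gives no number screened, no number excluded and no reasons. The 14 are women who completed between 1 and 5 sessions, which is not a count of women passing screening. A screening loss raises the number to be screened; it does not by itself cap enrolment.
- **That the viral load results cannot be interpreted.** Regression to the mean requires selection on viral load, which is not shown. If change is measured from the separate draw after enrolment, the bias is reduced. The article also limits viral load to feasibility of collection and a preliminary look at outcomes.

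It is also fair to say that suppression among suboptimally adherent women may be below the 25% background figure.

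**Conclusion.** The inconsistency is real. The aim 2 section and the Participants section name different tests for confirming HIV status at screening, and the viral load test does not fit women on ART. This is a stated rule that misfires if followed, not a detail left out by a condensed article.

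Its practical size is unknown. If viral load decided entry, the number to screen for 20 confirmed women would be 22, 27 or 40 at suppression of 5%, 25% or 50%. Those figures assume that an undetectable result leaves a woman unconfirmed and excluded, and that the chosen share applies to the target group; the article establishes neither. If OraQuick decided, there is no loss on this ground.

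This should be fixed, but it does not invalidate the pilot, which is a completed 1-arm feasibility study without a planned efficacy test. It matters because the Results section says the findings will inform further adaptation and a clinical trial, and readers need to know who could enter.

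**What to change.** **In the protocol text and any successor trial:** reconcile the two sections so that one antibody-based test, the OraQuick already named under Participants, confirms HIV status in both aims. State that the screening viral load does not determine eligibility, and what it is for if it is kept.

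**In the report of this pilot:** screening is over, so the text must describe what was done and not what would have been preferable. State which test was actually used to confirm status, whether viral load decided eligibility, and how many women, if any, were screened out on it. If any were, say so when presenting recruitment, and interpret viral load change as coming from women selected on a detectable value.

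**Cost:** a few sentences and a count from the screening log, if one was kept. Both tests are already in the plan, and no sample size changes.

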**Figure 1 figure1:**
[figure not shown]
SOAR study design. ART: antiretroviral therapy; SOAR: Speaking Out and Allying Relationships; STI: sexually transmitted infection; VL: HIV viral load.

### Procedures

#### Overview

Once enrolled, participants will complete a behavioral survey on REDCap. These measures cover HIV, sexuality, relationship stigma and discrimination, communication in relationships, and HIV prevention and treatment behaviors [47-53]. They will also complete syphilis testing using a rapid diagnostic test (Abbott Determine Syphilis TP), blood draw for HIV viral load, and urine collection for *Chlamydia trachomatis* and *Neisseria gonorrhea* testing. All measures will be administered by study staff.

Afterward, participants will receive training in Zoom, and their smartphones will be assessed and set up for Zoom compatibility. Participants will be notified that they will receive an SMS reminder 12 hours before each session, and then 1 hour before each session, they will receive an SMS with the Zoom link for that session. Also, participants will be informed that during the intervention they will be asked to complete an action plan, and they will receive a partner referral letter via SMS or in paper form (their choice) at the start of the study and can request the letter throughout the study. The referral letter describes the availability of local HIV and mental health services. Each participant will be informed that they will complete 1 SOAR session per week for 5 weeks with 2 check-in sessions afterward.

#### Group Check-Ins

All participants will be invited to attend group check-ins (n=2) via Zoom. The check-in dates and times will be provided during the last session with connection details (eg, Zoom link) sent via SMS to their mobile devices. Participants will be informed that they will receive a reminder about each check-in session 12 hours before and then 1 hour beforehand.

Each session and group check-in will be conducted by the study coordinator and a research assistant who is trained in the intervention*.*

#### Retention Procedures

All participants will be given a card with the study phone number to contact the interventionist if their phone number changes or if they have technical difficulties during the session (the card will not contain information that identifies their participation in the study). The interventionist will phone participants after a missed study visit and SMS each participant monthly to confirm smartphone numbers to support retention.

### Measures and Data Analysis

We will use the same measures as outlined in the parent study to include feasibility, behavioral outcomes for ART adherence and relationship communication, and HIV viral load.

#### Feasibility

The assessment of feasibility encompasses four domains: feasibility [54], acceptability [55], willingness [56], and safety [57]. Feasibility pertains to the ability to successfully recruit and retain participants, as well as facilitate message exchange and engagement in group sessions [54]. Acceptability refers to participants’ preferences and satisfaction with different components of the intervention [55]. Willingness relates to participants’ interest in enrolling in a longer study and their likelihood of recommending the intervention to others [56]. Safety focuses on ensuring the confidentiality and security of participant data and communication both within and outside the intervention.[57]

We will assess feasibility using surveys and interviews. The Self-Intervention Evaluation Form and the Client Satisfaction Questionnaire will be administered to evaluate the acceptability [58,59]. A study-specific Likert scale survey will also be developed to assess feasibility, willingness, and safety [60]. This survey will gauge participants’ perceived ability to exchange messages, participate in group sessions and check-ins (feasibility), their likelihood of enrolling in a longer study or referring other transgender women (willingness), their willingness to provide referral letters to partners, and their perception of the intervention’s confidentiality and security (safety). Also, we will conduct 30-minute interviews with purposively all participants, and these will be conducted at baseline, midintervention, and postintervention [61]. Feasibility will be evaluated by examining participants' attitudes toward various aspects of the intervention, such as video-group interactions, referral letters, and their perceived changes in self-management of ART, HIV risk, and HIV disclosure [62]. Acceptability will be assessed by examining participants’ preferences and satisfaction with specific intervention components and the intervention as a whole [62]. Willingness will be measured by assessing participants’ willingness to use the intervention consistently from start to finish, their openness to using the intervention in different contexts, and their likelihood of recommending the intervention to others [62]. Safety will be examined by evaluating participants’ perceived levels of discomfort with different intervention components and their perceptions of personal safety and the risk of unwanted disclosures [57].

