**Conclusions:**

Transgender women need more intervention options that engage their relationships since these can present barriers to HIV treatment outcomes like hindering viral suppression in South Africa. Delivering an existing yet tailored intervention via videoconference expands its reach to transgender women and allows them to engage with others and learn new skills in a secure setting like their homes. SOAR has the potential to improve relationship dynamics and reduce violence, which will in turn enhance HIV treatment and prevention engagement.

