To address this gap in interventions for transgender women living with HIV in South Africa, the aim of our study is to tailor our existing intervention, Speaking Out and Allying Relationships (SOAR) intervention, with them and then conduct a 1-arm pilot study to assess intervention feasibility in Eastern Cape, South Africa. Specifically, we will tailor SOAR and assess usability for content understandability and satisfaction (aim 1), and then evaluate its feasibility to include retention and any changes in behavioral and biomedical measures (aim 2). We hypothesize that participants will find SOAR feasible, acceptable, and safe to inform a larger efficacy study.

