Our SOAR intervention is based on Healthy Relationships (HR), a 5-session, group-based evidence-based intervention to develop individual HIV disclosure risk assessment and safer sexual behavior skills with partners that have demonstrated efficacy in these outcomes in a range of settings [33,34]. The core elements of SOAR are to: (1) develop coping skills to manage HIV-related stress and sexually risky situations; (2) enhance decision-making skills for HIV disclosure to partners; and (3) establish and maintain safer sex practices with partners. The HR intervention was identified based on our preliminary research with sexual minority men and transgender women in South Africa [35]. Additionally, through this preliminary research, we demonstrated that transgender women are willing to complete HIV-related group work and have an interest in mHealth tools, like videoconference modalities, to learn skills in HIV treatment management and disclosure for support [36,37]. Moreover, harnessing high use rates of smartphones by transgender women for intervention delivery is feasible in South Africa [20,38]. Increased evidence shows that transgender women access web-based social networking sites and use SMS for social networking through mobile and smartphone technologies, creating the potential to tag on ART adherence interventions [39,40]. In our research, we found that HIV-positive sexual minority men and transgender women regularly use videoconferencing to support community networking across rural and urban settings, with 2-hour conversation events focused on HIV, sexuality, and gender [37]. Further, mHealth tools (SMS, chat rooms, and web-based video group interventions) for HIV prevention and treatment in South Africa are part of the national strategic plan [41]. As in the original HR, our SOAR intervention integrates media, scenarios, and roleplays for skill development, and these reflect the experience of South African sexual minority men living with HIV and in relationships. In addition to the standard 5 sessions, we include three 30-minute booster sessions to review action plans over 3 months.

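### The pilot is to determine safety, but safety is defined by confidentiality and participants' perceptions, so partner violence and actual unwanted disclosure need not be counted

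*Protocol article*

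**What the plan says.** The section Evaluating the Feasibility of SOAR for Transgender Women gives the purpose of the one-arm pilot as "to determine feasibility, acceptability, willingness, and safety for transgender women".

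The Feasibility section, under Measures and Data Analysis, then says three things about the safety domain:

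- Definition: "Safety focuses on ensuring the confidentiality and security of participant data and communication both within and outside the intervention".
- Survey: a study-specific Likert questionnaire, whose safety items ask how confidential and secure participants perceive the intervention to be.
- Interviews: these are held with all participants before, during and after the intervention, and for safety they cover "perceived levels of discomfort with different intervention components and their perceptions of personal safety and the risk of unwanted disclosures".

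According to the Introduction, one core element of SOAR is to "enhance decision-making skills for HIV disclosure to partners". The Procedures overview adds a referral letter for partners, given at the start and available again on request. On the hazards, the Background says: "Fear of partner rejection or loss and intimate partner violence may lead transgender women to limit or halt ART use". The Theoretical Framework section also acknowledges that participants' relationships may carry a risk of violence.

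**The concern.** A safety outcome should be able to register the harms that the intervention could foreseeably cause. Here the article's own account points to what may happen between a woman and her partner once her HIV status is known or suspected. The stated definition reaches those harms only as perceptions, and none of its components is an event with a numerator and a denominator.

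At stake is the sentence that the pilot will hand to the next study. A report could follow the definition exactly, conclude that SOAR is safe, and give no number for partner violence or unwanted disclosure. Those planning the larger trial would then have a favourable label but no rate, and no bound on a rate, for the harms of most interest.

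**Working it through.** The article gives no safety rate, threshold or power, so it has no figure to reproduce. The check is mainly a reading of each listed measure against two events: partner violence, and an actual unwanted disclosure of HIV status.

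**Step 1. Does any listed measure count either event?**

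| Place in the article | Content | Counts an event as safety? |
|---|---|---|
| Feasibility, definition | Confidentiality and security of data and communication | No |
| Feasibility, survey | Perceived confidentiality and security | No |
| Feasibility, interviews | Perceived discomfort, personal safety, disclosure risk | No; incidents may surface in talk |
| Procedures, overview | Survey on stigma and discrimination, relationship communication, prevention and treatment behaviours | No violence measure listed |
| Relationship, ART Adherence, and Biomedical Measures | Satisfaction, communication, disclosure, adherence, viral load | No; disclosure is a behavioural outcome here |

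The last row needs care. HIV disclosure is surveyed, but as something the intervention supports. The article does not say that unwanted disclosures will be separated from chosen ones or passed to the safety domain.

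**Step 2. What happens to an incident raised in an interview?** The same section says that all data will be analysed by procedures similar to those of aim 1. The aim 1 Data Analysis section describes coding of transcripts and thematic analysis. Read literally, an incident would feed a theme, and nothing stated turns it into a count over enrolled women.

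**Step 3. Would a count be informative at this size?** Inputs: planned n = 4 groups × 5 = 20, which agrees with the stated N; and n = 14, the number of participants given in Results. The event rates are assumptions, because the article gives none.

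The chance of at least one event is 1 − (1 − p)^n:

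| Assumed true rate p | n = 20 | n = 14 |
|---|---|---|
| 5% | 64% | 51% |
| 10% | 1 − 0.9^20 = 88% | 1 − 0.9^14 = 77% |
| 20% | 99% | 96% |

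The exact one-sided 95% upper limit after zero events is 1 − 0.05^(1/n):

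- n = 14: 1 − 0.05^(1/14) = 19.3%
- n = 20: 1 − 0.05^(1/20) = 13.9%

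The upper ends of the two-sided exact 95% intervals, 1 − 0.025^(1/n), are 23.2% and 16.8%.

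A count would therefore probably show at least one event if the true rate were 10% or more. Even a clean count would leave rates of roughly one woman in seven (n = 20) or one in five (n = 14) compatible with the data.

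**The case against.** The strongest defence is that this is an article, not the full protocol. Social-harm or adverse-event reporting is commonly left to the full document, and the article imports its measures from a parent study that is not shown. That is right, and a reader should not infer that harms went unmonitored. The point does not depend on that. It rests on a definition the article states, and a separate log would not enter the safety result under that definition.

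A second defence is that the hypothesis is itself about perception: "We hypothesize that participants will find SOAR feasible, acceptable, and safe to inform a larger efficacy study". Perception measures suit that sentence. They do not suit the stated purpose of determining safety.

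Third, the personal-safety interviews cover all participants at three times. A reader might infer that a woman harmed after disclosing would be invisible if she rated confidentiality well. The article does not support this, because her interview is also safety data. What stands is narrower: the incident need not be counted.

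Three other strong readings also fail:

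- The Background names rejection, loss and violence as fears that may affect treatment use. It does not rank violence as the main hazard of disclosure.
- The abstract says "SOAR has the potential to improve relationship dynamics and reduce violence, which will in turn enhance HIV treatment and prevention engagement". This states a potential, not a result of the pilot, so it is not an unsupported finding.
- That harmed women would be the likeliest to drop out is plausible, but nothing in the article shows it.

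Finally, with one arm, background violence cannot be separated from harm caused by the intervention. That is true, and it limits what a count can mean. It does not justify leaving the count out.

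**Conclusion.** The concern holds in limited form. The article sets out to determine safety, but defines and measures it by confidentiality, security and perception. A conclusion that SOAR is safe could therefore be reached without a count of partner violence or of actual unwanted disclosure. The documents do not show that harms were ignored, only that the stated definition does not bring them into the result as events.

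This is a worthwhile, inexpensive improvement and not a flaw that undoes the pilot. The binomial limits apply to any yes/no outcome at these sample sizes, so they show how little zero events would prove and do not measure the defect itself. They assume one independent yes/no outcome per woman, full ascertainment, and 14 or 20 as the denominator. The Results section describes the 14 as women who had completed between one and five sessions, so the number enrolled should be confirmed.

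**What to change.** **Definition.** In the Feasibility section, add to the safety domain the number and proportion of all enrolled women with (a) reported partner violence and (b) an actual unwanted disclosure of HIV status. List the two separately, each with an exact 95% confidence interval and the number of women not ascertained. Collect them through the interviews already planned before, during and after the intervention. Label the existing survey and interview items perceived safety.

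**This pilot.** Testing was completed in January 2025, so new questions cannot be added. Tabulate any such incidents already recorded in interviews or study logs, state that ascertainment was not systematic, and limit the conclusion to perceived safety. Carry the event-based definition into the next trial.

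**Cost.** Some tabulation work now and a few more interview questions later. The safety statement becomes more cautious, and a one-arm count still cannot attribute violence to the intervention.
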